### Setting

This trial will take place at an outpatient psychiatric institute in Québec, Canada.

### Participants

#### Sampling

Our primary *inclusion criteria* are that the participants must (1) self-identify as Inuk, (2) live in the city where the study is taking place, (3) be aged between 14 and 60 years of age, and (4) be proficient in English or French.

With exclusion criteria, we confirm safety and best fit with the study necessitating VR and psychophysiological equipment use. We exclude those who do not identify as Inuk, youth aged <14 years, and adults aged >60 years, as well as individuals who do not tolerate VR headset and study sensors. We exclude individuals with a self-reported history of psychosis or schizophrenia, with current substance abuse as measured by screens (score >8 on the Alcohol Use Disorders Identification Test C (AUDIT-C) or >3 on the Drug Abuse Screen Test), or with any change in psychoactive medications 4 weeks before screening. In addition, we exclude individuals with physical conditions that might cause risks during VR use (ie, history of cardiac condition or epilepsy). There are no exclusions based on other concomitant care.

Meeting the diagnostic criteria for any specific disorder, verified history of trauma, or trauma symptoms was not part of our inclusion and exclusion criteria, given our focus on cultural sensitivity, our chosen skills-building approach in the therapy manual, and the shared history of trauma by community members.

#### Sample Size

There is, to our knowledge, no estimate of the effect size of emotion regulation–based VR interventions among Indigenous populations, and this proof-of-concept study will be necessary for accurate estimation of power in future trials. As described in the previous section, mental health risks among Indigenous and Inuit populations differ from those among the general population, which emphasizes the need for this proof-of-concept study specifically in this population for power calculations in future work. However, a previous VR intervention for anxiety disorders among a general population sample had an estimated effect size of g=0.78 (medium) compared with minimal-attention controls and g=0.90 (large) with no-treatment controls [26,27]. To attain statistical power >90% with an alpha of *P*<.5, the sample size of n=20 in the active treatment group and n=20 in the active control group is sufficient for generalized linear models with a similar effect size (power=0.97; *df*=38; *P*=.05).

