## Methods

### Design

The study design is a 2-arm proof-of-concept RCT co-designed with an Inuit advisory committee. The first treatment arm (A) is a 10-week VR-CBT. An active control treatment with minimal attention; the second treatment arm (B) will be using Calm Place as a 10-week self-management. There will be no crossover between conditions, and we will use a 1:1 ratio randomization procedure. The protocol is described in accordance with the SPIRIT (Standard Protocol Items: Recommendations for Interventional Trials) guidelines for interventional trials and is detailed in Multimedia Appendix 1. Ultimately, the goal of the study is to establish the initial feasibility of the VR-CBT and the technologies used and to identify the best measures for initial efficacy.

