##### Calm Place as the Active Control

During the use of the VR application, the Calm Place user may see flowing water, mountains, and tree cover; a tropical atoll with sand, palm trees, and the ocean; or an arctic scene with large pines, snow cover, and large stones. In Calm Place, each virtual environment offers applications [25,28], such as visual breathing aids, time and weather cycles, and meditation voice overs, with the guidance of the VR program. Here, the guidance on relaxation is nonpersonalized and is based on the selections of the user within the VR environment. Thus, though participants’ weekly choices regarding prevalence and duration of use are self-managed and done from their home, this intervention involves guided programming for guidance. The self-management program—Calm Place—does not have any avatar, social-interactive, or personalized components. The research team will contact these minimal-attention control participants weekly to check whether they use the application and to verify their safety.

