### Strengths and Limitations

The process of cultural adaptation of psychotherapy was conducted to increase acceptance. The advisory committee recommended study inclusion based on sociocultural background, not trauma symptoms, to improve the cultural safety of the trial. Accordingly, inclusion is based on subjective motivation for improved mental health rather than any categorical diagnosis or subjective or objective need for treatment. In addition, the content of the psychotherapy was modified to confirm safety, according to the comments from the advisory committee. These modifications include reducing exposure and distress-producing exercises and removing the homework normally part of the therapy. A limitation is that these changes may challenge the odds of a psychotherapeutic response.

In our study protocol, we included an active control group, noting the vulnerability of the study population; this may lead to reduced between-group effects. However, only the active treatment is culturally adapted and guided by a psychotherapist, which could improve attendance and thus long-term efficacy in the active treatment group. We will observe the impact of the setting as compared with the content on acceptance while asking for the preference for therapist-guided or self-management treatment. This proof-of-concept RCT will inform us about the potential challenges or limitations of the study protocol, and we can characterize the best outcome measures and calculate power for the further efficacy trial. We consider the scientific risks acceptable, given the extreme imbalance between the need and availability for access to valid and safe treatments.

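### The stated power of 0.97 does not follow from the printed inputs: 20 per arm, df=38 and alpha .05 give 0.67 two-sided at g=0.78 (unadjusted), and the same sentence prints two alphas

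*Protocol article*

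**What the plan says.** The Sample Size section takes its benchmark from earlier work on VR for anxiety disorders, which "had an estimated effect size of g=0.78 (medium) compared with minimal-attention controls and g=0.90 (large) with no-treatment controls". It sets the target and the test level with "To attain statistical power >90% with an alpha of *P*<.5", says that "the sample size of n=20 in the active treatment group and n=20 in the active control group is sufficient", and supports this with the phrase "sufficient for generalized linear models with a similar effect size (power=0.97", followed by df=38 and P=.05. Allocation is equal: under Design, "we will use a 1:1 ratio randomization procedure".

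Two other places bear on the benchmark. The section on Calm Place as the Active Control describes the comparator in these terms: "The research team will contact these minimal-attention control participants weekly". Strengths and Limitations says of the active control that "this may lead to reduced between-group effects".

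The Sample Size section does not state whether the test is one- or two-sided, what within-person correlation is assumed, or what attrition is allowed for.

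**The concern.** Sample size, standardized effect, degrees of freedom and test level are all printed, so the power can be checked directly. The result falls well short of 0.97 and short of the 90% target. Two test levels that differ tenfold stand in one sentence, so a reader cannot tell which one the figure refers to.

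This matters although the trial is a proof of concept. Such a trial need not be powered for efficacy, but this one claims that it is. DERS-16 is a named primary outcome with a between-group model. A stated power of 0.97 tells the reader that an effect of the cited size would be missed 3 times in 100; on the printed inputs, read as an unadjusted two-sided comparison, it is 33 in 100. A non-significant DERS-16 comparison could then be read as far more conclusive than it is. The trial is also meant to inform the power calculation of a larger one, and a wrong figure here is a poor starting point.

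**Working it through.** **Inputs.** From Sample Size: 20 per arm, g=0.78 (minimal-attention controls) and g=0.90 (no treatment), P=.05, df=38. Calm Place participants are called minimal-attention controls, so g=0.78 is the matching value. No SD is needed because the effect is standardized. Sidedness is not stated, so both versions are shown.

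**Formula.** For a two-sample t test, df = 20 + 20 − 2 = 38 and the noncentrality is d × √(20×20/40) = d × √10 = 3.162d. Power is the probability that a noncentral t with these values exceeds the critical value: 2.024 in absolute value for two-sided .05, or 1.686 for one-sided .05.

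**Attempt to reproduce 0.97.**

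| d | noncentrality | two-sided .05 | one-sided .05 |
|---|---|---|---|
| 0.60 | 1.897 | 0.46 | 0.59 |
| 0.78 | 2.467 | 0.67 | 0.78 |
| 0.90 | 2.846 | 0.79 | 0.87 |

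The row for d=0.60 is an illustrative smaller effect, not one the protocol cites. The stated figure is not reproduced with either cited effect or either sidedness.

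**What 20 per arm can detect** (df=38, alpha .05):

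| power | d, two-sided | d, one-sided |
|---|---|---|
| 0.80 | 0.91 | 0.80 |
| 0.90 | 1.05 | 0.94 |
| 0.97 | 1.25 | 1.14 |

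**Size of the gap in participants.** At d=0.78, two-sided .05 and before attrition, 90% power needs 36 per arm and 97% needs 50 per arm.

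**Attrition.** No rate is given. Assuming 20% to 25% loss, 16 or 15 per arm would be analysed, and the unadjusted power at d=0.78 is 0.57 or 0.54.

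**Could the planned model reach 0.97?** The Data Analysis section plans a mixed model of repeated DERS-16 scores. Adjusting for baseline with pre-post correlation r makes the effective d equal to d/√(1−r²). The correlations below are assumptions.

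| r | effective d | power, two-sided .05 |
|---|---|---|
| 0.5 | 0.78/0.866 = 0.90 | 0.79 |
| 0.7 | 0.78/0.714 = 1.09 | 0.92 |
| 0.8 | 0.78/0.600 = 1.30 | 0.98 |

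A change-score analysis, which also has 38 df, uses d/√(2(1−r)). At r=0.5 this leaves d at 0.78 and power at 0.67; at r=0.8 it gives 0.78/0.632 = 1.23 and power 0.97.

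**Precision.** The approximate 95% half-width for d is 1.96 × √(1/20 + 1/20 + d²/80). This is 0.62 at d=0 and 0.64 at d=0.78, so about 0.63.

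**The case against.** The strongest defence is that 0.67 belongs to an unadjusted comparison at one time point, whereas the plan is a repeated-measures model. With a high enough within-person correlation that model could reach 0.97, and df=38 fits a two-group change score as well as a simple two-group test. The DERS-16 section even reports a retest reliability of r=0.88. This part stands to the extent that 0.67 must be labelled an unadjusted benchmark. It does not rescue the printed figure: the power statement invokes no correlation, and retest reliability is not a pre-post correlation over a 10-week treatment.

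A second defence is the trial's purpose. The protocol limits itself to feasibility, effect estimation and planning of a later trial, and nowhere says that a null DERS-16 result would count against VR-CBT. That tempers the consequence but does not make the number right.

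Some stronger readings are tempting, and the protocol does not support them:

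- *The true chance of missing the effect is at least 33%.* This is not a lower bound. Adjustment could reduce it; attrition or a smaller effect would raise it.
- *The source of the error is known.* A two-sided alpha of .5 at g=0.78 gives 0.964, and entering d/2=0.39 as f² in a linear model with 1 and 38 df gives 0.9705. Both are near matches, but nothing in the text shows that either slip occurred, and .5 may simply be a misprint.
- *The protocol expects a smaller effect than the benchmark.* It says only that the active control may reduce between-group effects, and g=0.78 is already a value against minimal-attention controls.

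**Conclusion.** The power statement is wrong as written. At alpha .05 no printed input gives 90%, let alone 0.97. The unadjusted benchmark is 0.67 two-sided (0.78 one-sided) at g=0.78 and 0.79 (0.87 one-sided) at g=0.90, and the two printed alphas contradict each other. This rests on a t test with equal arms of 20, all analysed; two-sidedness is an assumption, but the conclusion is the same one-sided. It does not establish the power of the planned mixed model, which depends on a correlation that the power statement does not give. It is no objection to n=40 as such.

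**What to change.** In the Sample Size section, keep n=40 and make these changes:

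- State one test level, .05 two-sided.
- Delete the claim of more than 90% power and the figure of 0.97.
- Give the benchmark, labelled as an unadjusted two-group comparison before attrition: power 0.67 at d=0.78 and 0.46 at d=0.60, with d=0.91 the smallest effect detectable with 80% power.
- Quote a higher figure for the repeated-measures model only together with its assumed within-person correlation and attrition, for example 0.79, 0.92 and 0.98 with baseline adjustment at d=0.78 and correlations of 0.5, 0.7 and 0.8, before attrition.
- Present the between-group DERS-16 effect as an estimate with a 95% confidence interval (half-width for d about 0.63), and state that a non-significant result is not evidence of no effect.

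The protocol gives no feasibility rationale for 40 participants, so the corrected text should not supply one unless the sponsor confirms that it was the reason. The cost is a text correction and a less favourable stated power; no participants are added.

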### Procedure

#### Recruitment

The research team will recruit participants who are potentially willing to participate in either of the 2 arms of the trial. Recruitment methods will include word of mouth, flyers, and posts on social media, websites, and Montreal neighborhoods. First contacts with potential participants will involve informing them about the study and screening for initial eligibility criteria (eg, aged 14-60 years, having no acute medical or psychological risks, etc). First contacts will be done to further explain the study protocol and evaluate the eligibility criteria with potential participants. This can occur over the phone, via secure email, or in person. Our eligibility criteria include screening for suicide risk and higher scores on alcohol and drug measures. This screening will occur in person during the first visit to enroll in the study or via telephone. Once eligibility and interest in the study are established either in person or via telephone, the participants can proceed to the informed consent process with our team (in person).

#### Randomization and Masking

After receiving informed consent for participation, a research assistant will use a computerized randomization generator to randomly assign participants in a simple 1:1 ratio (VR-CBT or Calm Place). Before randomization, we will show participants the treatment rationales, explaining the 2 possible study groups. They will report their preference for either treatment in a forced-choice question, rate their preference for each treatment on a scale from 1 to 10, and provide comments on why they selected this choice. This information is collected to inform future larger trials and clinical services. The treatment cannot be supplied blinded to the content. However, as the measurements are self-reports and objective measurements, we do not use blinded outcome evaluation. Once random assignments are decided, they will be kept hidden from researchers and research assistants until the participants begin the trial.

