**Methods:**

Trial participants will be randomly assigned to an active condition or active control condition in a 1:1 ratio. Inuit aged 14 to 60 years will receive a culturally adapted and therapist-guided VR-CBT with biofeedback or a VR relaxation program with nonpersonalized guided components over a 10-week period. We will collect pre- and posttreatment measures of emotion regulation and biweekly assessments over the treatment and at 3-month follow-up. The primary outcome will be measured by the Difficulties in Emotion Regulation Scale (DERS-16) and a novel psychophysiological reactivity paradigm. Secondary measures include psychological symptoms and well-being via rating scales (eg, anxiety or depressive symptoms).

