### Materials

To support the delivery of the interventions and the corresponding collection of data during the trial, a sensor management system and web-based clinician portal were developed in collaboration with the National Research Council Canada (DJ and CP). The sensor management system facilitates the connection and initialization of the biofeedback sensor, eVu TPS (Thought Technology Ltd) as well as the streaming of data to the web portal. The web portal allows the management of participant sessions as well as live and postsession biofeedback data visualization. The raw biofeedback data (in CSV format) are also available through the portal to study coordinators and clinicians for postprocessing and analysis.

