#### Objective Psychophysiology Data Analyses

To accurately identify peaks and not simply gradual increases in skin conductance observed over time, we will filter skin conductance data with a threshold value of 0.04 µS and average over 5 seconds [81,82]. As our study involves movement in a VR space in addition to exposure to a potential stress-inducing situation, we will filter the data with a lower limit of 40 bpm and an upper limit of 200 bpm [83]. Heart rate will also be averaged over 5 seconds. Following averaging, we will use open-source filters for preprocessing the data; then, the psychophysiological data will be processed with existing packages in MATLAB and Python. To correlate the DERS-16 and secondary outcome measures (CORE, WEMWBS, GAD-7, PHQ-9, and PC-PTSD-5) with psychophysiological data, we will employ nonparametric regression analyses in R Statistical and Computing Software. In addition, we will explore preliminary cutoff sum scores for therapeutic response by plotting receiver operating characteristic curves and conducting AUC analyses. We will also compare baseline to postintervention (second baseline) changes in psychophysiology using regression models. Cohen *d* or nonparametric tests will calculate the effect size between groups A and B.

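### The stated reason for waiving blinded outcome evaluation does not cover the derivation of the psychophysiological primary outcome, which could be processed from coded files at little cost

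*Protocol article*

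**What the plan says.** The abstract of the protocol article gives the primary outcome two parts: "The primary outcome will be measured by the Difficulties in Emotion Regulation Scale (DERS-16) and a novel psychophysiological reactivity paradigm".

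On masking, Randomization and Masking makes three statements. Treatment is open: "The treatment cannot be supplied blinded to the content". Blinded evaluation is waived, with a reason: "as the measurements are self-reports and objective measurements, we do not use blinded outcome evaluation". Assignments are concealed for a limited time: "they will be kept hidden from researchers and research assistants until the participants begin the trial".

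On signal processing, Objective Psychophysiology Data Analyses fixes two rules. For skin conductance, "we will filter skin conductance data with a threshold value of 0.04 µS and average over 5 seconds". For heart rate, "we will filter the data with a lower limit of 40 bpm and an upper limit of 200 bpm", again with 5-second averaging. The next step is described only as "we will use open-source filters for preprocessing the data", followed by MATLAB and Python packages that are not named.

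On access, Materials says of the sensor portal: "The raw biofeedback data (in CSV format) are also available through the portal to study coordinators and clinicians for postprocessing and analysis".

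**The concern.** The waiver treats two kinds of measurement alike. When a participant who knows the arm completes DERS-16 or a visual analog scale, the participant is the assessor and the assessment is unblinded. That is unavoidable here. A physiological recording is different, because a later step turns the raw trace into an outcome value and that step can be done without knowing the arm. Calling the measurement objective describes the sensor and does not describe the choices made between the trace and the number that is analysed.

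This matters for three reasons. The reactivity paradigm is the only part of the primary outcome for which any step can be masked. Research Aims makes the feasibility and validity of these measures as objective outcomes a goal of the trial. The effect sizes are meant to inform a larger trial, and the team running this one developed one of the two interventions. If processing choices are made with the arm in view, the claim to objectivity is weaker than it needs to be, and any distortion would carry over into the planning of the next trial.

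**Working it through.** The point rests on no figure of the plan, so the check sets the relevant sections side by side.

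1. **Is the reactivity measure part of the primary outcome?** Yes. The abstract says so, and Objective Measures stands under Primary Outcome Measures.

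2. **Who may know the arm when the signals are processed?** Concealment ends when participants begin the trial. After that, therapists deliver VR-CBT, and the research team contacts Calm Place participants every week (Calm Place as the Active Control). No section withholds the arm from those who process or analyse signals.

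3. **How much of the processing is fixed?**

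| Step | Status in the article |
|---|---|
| Skin conductance threshold | Fixed, 0.04 µS |
| Heart rate limits | Fixed, 40 and 200 bpm |
| Averaging | Fixed, 5 seconds, both signals |
| Nominal segment durations (Objective Measures) | Fixed: 3, 5.5, 5.5, 3 and 10 minutes |
| Preprocessing filters | Open source, not named |
| Packages and settings | MATLAB and Python, not named |
| Handling of shortened or abandoned plank segments | Not stated |

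4. **Why does the last row matter?** Objective Measures sets 5.5 minutes of walking on the plank, but lets a distressed participant stay for 2 minutes without walking, or withdraw. With 5-second averaging, a full segment gives 5.5 × 60 / 5 = 66 averages. If the 2 minutes replace the whole walk, which is an assumption because the text does not say, the segment gives 2 × 60 / 5 = 24. Someone must decide whether such a record is used, cut or left out.

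5. **How many records are affected?** Sample Size plans 20 + 20 = 40 participants. Objective Measures limits the repeat test to those who completed 7 to 10 sessions, so 40 is a ceiling for post-treatment records.

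6. **Is masked processing practical?** The baseline measurement section says data are stored under research IDs, so files without arm labels need no new coding system.

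**The case against.** The strongest reply has four parts.

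- **This is a condensed article.** File coding, analyst masking and data lock commonly sit in a full protocol or analysis plan. That is right as far as it goes, and the lack of such detail alone would be no finding. But the article states a rule and a reason for it, and the reason is what fails.

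- **The main thresholds and segment durations are already set, and packaged software leaves less room for judgement.** This stands as a limit on the size of the problem. It does not close the open rows in the table. A reader might infer that all processing is discretionary, including artefact rejection, segment marking and choice of cutoffs. The article does not support that: it names neither of the first two as a manual step, and the cutoffs it plans to explore are sum scores for therapeutic response, not signal thresholds. Nor does every listed metric pass through the open steps. Blood pressure comes from a separate device, and processing rules are given only for skin conductance and heart rate.

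- **The portal passage may not concern the outcome.** A reader might infer from Materials that coordinators and clinicians derive the reactivity outcome knowing the arm. The text speaks of biofeedback data, describes a system that supports delivery of the interventions as well as data collection during the trial, and grants access without assigning the task. The reactivity recordings may be included, but the article does not say so. The point does not depend on it.

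- **Masked processing leaves much untouched, and this is a 40-person proof-of-concept study.** Both are true. They limit the benefit claimed and make this a modest improvement, but they do not repair the reason given for the waiver.

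**Conclusion.** The waiver is explicit, and its reason does not extend to the derivation of the psychophysiological part of the primary outcome. Some rules are fixed, others are open, plank records can differ between participants, and nothing stated keeps processors or analysts unaware of the arm. The document does not show that biased processing will occur. It shows that a step which could be masked has been waived on a ground that does not apply to it.

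The size of any bias cannot be calculated from the document. The exposure is at most 40 post-treatment reactivity records, through the steps left open. The conclusion assumes that the unnamed filters and packages leave some room for choice. If they were fully specified elsewhere before any data were seen, the remaining room would be small. Masked processing would not protect DERS-16, the visual analog scales or the way the test is run.

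**What to change.** Limit the waiver in Randomization and Masking to self-report and test administration. Then state the following:

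- Reactivity recordings, baseline and post-treatment, are processed under research IDs with no arm label, by existing staff who do not use the allocation list.
- The filters, packages and settings, and the rules for excluding or truncating records (including incomplete plank segments), are written down and locked before arms are unmasked.
- The derived data are locked before arms are unmasked.
- As a limitation, self-reports and the conduct of the reactivity test remain unblinded.

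It would also help to say in Materials whether the reactivity recordings pass through the portal and who derives the outcome from them.

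The cost is a file-handling rule and a data-lock step. No extra visit or participant burden is needed. The documents give no cost figure, so this should be called low cost rather than free. In a small team, the processing should go where possible to someone who neither delivers the therapy nor makes the weekly calls, because an ID may otherwise be recognised.
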